### Statistical analysis

The statistical significance level will be set at 5%, and the data will be processed with the last observation carried forward method for the intention-to-treat analysis. Statistical analysis in this study will be performed using IBM SPSS Windows version 19.0 statistical software (IBM Co., Armonk, NY, USA) and will be based on the Korean Clinical Trial Statistics Guidelines.

The study will identify the comparative equivalence of demographic variables and clinical characteristics between the experimental and control groups by performing the two sample t-test or Mann-Whitney U test if normality test is satisfied or not for continuous data, chi-square test for categorical data.

A repeated measure two-factor analysis will be performed to identify differences in VAS, blood perfusion, frequency and duration of cold hands sensation attacks and HRV scores between the experimental and control group based on time (baseline, weeks one, three, and five). If the interaction between group and time is statistically significant, the point at which the pattern of results between the two groups changes will be checked using the contrast analysis. To compare groups and the incidence frequency of adverse events related to acupuncture and medication, the chi-square test will be used.

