## Methods/Design

### Design

The study is a randomized controlled pilot clinical trial. It is designed to obtain basic information of a further full-scale trial about acupuncture treatment in subjects with cold hands sensation. The protocols to be used adhere to the principles of the Declaration of Helsinki and have been approved by the Institutional Review Board of Daegu Catholic University Hospital (approval number IORG0004453), where the study will take place. The trial is registered with the Korean Clinical Research Information Service (CRIS) registry. Written informed consent will be obtained from each participant before any treatment is given.

The outcome assessments and statistical analyses will be performed by professionals blinded to the assignment of subjects. The trial process is presented in Figure 1. The trial will run for five weeks. Subjects will be randomly allocated to one of two groups, a control group, in which subjects will receive only medication for three weeks, and an experimental group, in which subjects will receive the same medication as well as nine acupuncture sessions (three sessions per week for three weeks). Assessments will be made at baseline and again at one, three, and five weeks thereafter. The five-week assessment will be performed two weeks after treatment cessation. This study will be conducted between late November 2013 to February 2014 which is winter season in South Korea. We will record room temperature to control for temperature bias in this clinical trial.

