### Participants

A target sample size of 14 subjects with cold hands sensation has been set. One of the main objectives of this study is to provide an estimate of the sample size required for the full-scale randomized controlled clinical trial.

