### Interventions

Subjects will be randomly divided into two treatment groups: an experimental group (acupuncture plus medication group) and a control group (medication only group). The medication will be administered every day for three weeks and the acupuncture sessions performed three times per a week for three weeks (nine times in total). There are no other interventions such as moxibustion, exercises, or lifestyle advice in this study.

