**Table 1 Tab1:** **Schedule of treatments and outcome measurements throughout the five-week randomized controlled trial**

		Baseline	Treatment period									Follow-up period	
		Week 0	Week 1			Week 2			Week 3			Week 4	Week 5
Measurement	VAS	√	√						√				√
	Blood perfusion	√	√						√				√
	Frequency and duration of cold hands episodes	√	√						√				√
	HRV	√	√						√				√
Treatment	Medication		√			√			√				
	Acupuncture		√	√	√	√	√	√	√	√	√		

HRV: Heart rate variability, VAS: visual analogue scale.

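### Carrying the last observation forward would enter on-treatment scores at the off-treatment week-5 visit for anyone lost after week 3; the resulting bias is conditional on dropout and of unknown size and sign

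*Protocol article*

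**What the plan says.** Under Statistical analysis the article fixes the handling of missing data: "the data will be processed with the last observation carried forward method for the intention-to-treat analysis". It names no other method. The completed data then go into the main comparison: "A repeated measure two-factor analysis will be performed to identify differences in VAS, blood perfusion, frequency and duration of cold hands sensation attacks" and heart rate variability, over baseline and weeks 1, 3 and 5. If the group-by-time interaction is significant, contrasts are used to find where the two groups part.

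The schedule comes from three places:

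- Visits (Design): "Assessments will be made at baseline and again at one, three, and five weeks thereafter".
- Treatment (Interventions): "The medication will be administered every day for three weeks and the acupuncture sessions performed three times per a week for three weeks".
- Status of the last visit (Design): "The five-week assessment will be performed two weeks after treatment cessation".

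Table 1 agrees: no treatment is marked after week 3, and weeks 4 and 5 are labelled as follow-up. Under Withdrawal and dropout, participation ends on refusal, withdrawn consent, or breach of the criteria or protocol, so later visits may be missing. No dropout rate is given. On size, "A target sample size of 14 subjects with cold hands sensation has been set" (Participants), and the same section names sizing the full trial as a main aim.

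**The concern.** Weeks 1 and 3 are on treatment and week 5 is off treatment. LOCF ignores that boundary.

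- **Lost after week 3.** The end-of-treatment score is reused as the week-5 score. Persistence of whatever was seen at week 3 is assumed rather than measured.
- **Lost after week 1.** The week-1 score stands at weeks 3 and 5, although most of the course came later.
- **Lost before week 1.** The baseline score stands throughout.

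The interaction test and the contrasts look at the shape of the response over time, and LOCF flattens that shape for each affected subject. The filled values also count as observed, so the standard errors take no account of the imputation.

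What is at stake is the group difference at weeks 3 and 5 and the time pattern. These are the estimates that a pilot hands on to the design of the full trial.

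**Working it through.** The plan states no figure on this point, so there is none to reproduce. The check is the expected error that LOCF adds to the difference in mean VAS, experimental minus control (E − C); a negative error favours acupuncture.

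**From the article:** 14 subjects; visits at weeks 0, 1, 3 and 5; treatment to week 3.

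**Assumed:** 7 per arm (the ratio is not stated); 0 to 2 losses per arm; loss unrelated to outcome; the VAS paths below.

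**Formulas.** Let E1, E3, E5 and C1, C3, C5 be the true arm means at weeks 1, 3 and 5. Let pE, pC be the shares lost between weeks 3 and 5, and qE, qC the shares lost between weeks 1 and 3.

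- Week-5 error = pE(E3 − E5) − pC(C3 − C5)
- Week-3 error = qE(E1 − E3) − qC(C1 − C3)

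One loss is 1/7 = 14% of an arm, so it moves that arm's mean by one seventh of the change between the carried and filled visits.

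**Week 5, no true difference, both arms 6/5/4/5 (weeks 0/1/3/5).**
- Two lost in E after week 3: (2/7)(4 − 5) = −0.29
- Two lost in C instead: +0.29
- Equal losses: 0

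**Week 5, no true difference, both arms 6/5/4/5.5.**
- Two lost in E: (5 × 5.5 + 2 × 4)/7 = 5.07 against 5.50, error −0.43

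**Week 5, effect at week 3 that is gone by week 5: E 6/5/3/5.5, C 6/5.5/4.5/5.5 (true week-5 difference 0).**
- Two lost in E: (2/7)(3 − 5.5) = −0.71
- Two lost in C: −(2/7)(4.5 − 5.5) = +0.29
- One lost in each arm: (1/7)(−2.5) − (1/7)(−1.0) = −0.21, so equal losses do not by themselves remove the error

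**Week 5, effect fully sustained: E 6/5/3/3, C 6/5.5/4.5/4.5.**
- Any loss after week 3: error 0, because nothing changes between the two visits

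**Week 3, paths E 6/5/3/5.5 and C 6/5.5/4.5/5.5 (true difference −1.50).**
- Two lost in E after week 1: −1.50 + (2/7)(5 − 3) = −0.93
- Two lost in C after week 1: −1.50 − (2/7)(5.5 − 4.5) = −1.79

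The week-3 results count as errors only if the lost subjects would have followed the completers' path, that is, if the target is the effect had treatment continued. Suppose instead that the target is the effect regardless of stopping, and that a subject who stopped after week 1 would have stayed at the week-1 score. Then LOCF is right at week 3. A missing-at-random model that credits the subject with completer-like improvement is the one in error: on the 6/5/4/5.5 path, by about (2/7)(4 − 5) = −0.29 for two losses in E.

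The week-5 case for a subject lost after week 3 does not have this ambiguity. The course is over by then, and the true week-5 state is off treatment under either target.

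**Against the noise.** For an assumed VAS SD of 1.5 to 2.5 cm, the standard error of a 7-versus-7 difference is SD × √(2/7) = 0.80 to 1.34 cm. An error of 0.29 is then about 0.2 to 0.4 of a standard error, and 0.71 about 0.5 to 0.9.

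**The case against.** The strongest case on the other side has four parts.

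- **The harm is conditional.** Follow-up lasts five weeks, and the inclusion criteria require availability throughout, so few or no visits may be missing. With none missing, LOCF does nothing. This stands.
- **The size is assumed.** The article gives no dropout rate, VAS path or SD. Two losses in one arm and none in the other is a 29% to 0% split, and under the assumed SDs the resulting error is below one standard error. This stands, and is why the results are given as a range that includes zero.
- **The week-3 part depends on the target.** The hypothesis names no time point and does not say how stopping treatment is to be treated. This stands and confines the firm part of the point to week 5.
- **It is a small pilot.** The article acknowledges the small sample as a limitation. This lowers the priority but does not make the rule suitable, since the pilot's estimates are meant to inform the full trial.

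A separate analysis plan might add sensitivity analyses, and their absence from an article is no fault. It does not change the point, because the article states the method rather than leaving it open.

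A reader might infer that the intention-to-treat comparison is biased as it stands, or biased towards acupuncture because that arm has nine extra sessions to attend. The article supports neither. It says nothing about dropout by arm, and the error changes sign with the arm that loses subjects.

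**Conclusion.** The point holds in a limited form. LOCF is fixed for the intention-to-treat analysis. For any subject lost after week 3, it puts an on-treatment score in an off-treatment visit and treats it as observed in the group-by-time test and contrasts. For a subject lost after week 1, whether the frozen score is wrong at week 3 depends on a target that the article does not state.

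LOCF cannot be defended here as conservative, since the error can go either way. With two losses in one arm of 7, the week-5 error is about 0.3 to 0.7 cm for post-treatment changes of 1 to 2.5 cm, and nil if scores stay flat. The true size and direction cannot be determined from the article. The understatement of standard errors follows from single imputation, but its amount was not calculated.

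This should be fixed as a cheap improvement. Calling it a defect that invalidates the trial would go beyond the evidence.

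**What to change.** Replace LOCF as the primary method with a linear mixed model fitted by likelihood to all observed values, with group, visit and their interaction.

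- Keep baseline in the outcome vector, so that every randomised subject contributes, including one with no later visit.
- Use a parsimonious covariance structure and a small-sample degrees-of-freedom correction; 14 subjects will not support more.
- State that the model assumes data missing at random, and say whether the target is the effect regardless of stopping treatment.
- Report missing visits by arm, visit and reason.
- Keep LOCF, and for week 5 an analysis that returns missing scores to the subject's baseline, as labelled sensitivity analyses only. Both are single imputations and share the neglect of imputation uncertainty. Their use is to show how far the week-5 result moves between no change and full return.

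The cost is limited to the analysis: no new subjects, visits or measurements. Intervals may be wider. Because the article reports recruitment as finished, the change should be documented and dated.

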**Methods/Design:**

The proposed study is a five-week pilot RCT. A total of 14 subjects will be recruited and randomly allocated to two groups: an acupuncture plus medication group (experimental group) and a medication-only group (control group). All subjects will take nifedipine (5 mg once daily) and beraprost (20 mg three times daily) for three weeks. The experimental group will receive additional treatment with three acupuncture sessions per week for three weeks (nine sessions total). The primary outcome will be measured using a visual analogue scale. Secondary outcomes will be measured by blood perfusion in laser Doppler perfusion imaging of the hands, frequency and duration of episodes of cold hands, and heart rate variability. Assessments will be made at baseline and at one, three, and five weeks thereafter.

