### Hypotheses

In this randomized controlled two-arm clinical trial, we will evaluate the acupuncture treatment as an adjunct therapy to cold hands sensation. The hypothesis is that the addition of acupuncture treatment to medication reduces the severity of cold hands sensation (measured using a visual analogue scale (VAS)) significantly more than medications alone.

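### The directional VAS hypothesis is tested through a 3-df group-by-time interaction that has baseline as a time level: valid, but often inefficient, and it guarantees no single effect estimate for sizing the full trial

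*Protocol article*

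**What the plan says.** All references are to the protocol article.

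- **Hypotheses:** the claim has one direction, that "the addition of acupuncture treatment to medication reduces the severity of cold hands sensation", measured by VAS, more than medication alone does.
- **Data collection and the VAS subsection:** VAS is the primary outcome at baseline and weeks 1, 3 and 5. No week is named as primary.
- **Design and Table 1:** treatment lasts three weeks. "The five-week assessment will be performed two weeks after treatment cessation".
- **Statistical analysis, test:** "The statistical significance level will be set at 5" per cent, and a two-factor repeated-measures analysis looks for differences "between the experimental and control group based on time (baseline, weeks one, three, and five".
- **Statistical analysis, gate:** "If the interaction between group and time is statistically significant", contrasts are then used to find where the groups diverge. This is the only decision step described.
- **Statistical analysis, baseline:** "The study will identify the comparative equivalence of demographic variables and clinical characteristics between the experimental and control groups", by t-test or Mann-Whitney test for continuous data and chi-square test for categorical data.
- **Participants:** "A target sample size of 14 subjects with cold hands sensation has been set", and estimating the sample size of the full-scale trial is given as a main objective.

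**The concern.** The hypothesis can be answered by one number, the difference in VAS between arms at a stated time. The interaction test does not give that number. With two groups and four visits it has (2 − 1) × (4 − 1) = 3 degrees of freedom and no direction. It responds to any departure from parallel profiles, including patterns unrelated to the hypothesis, and it treats two on-treatment visits and one off-treatment visit alike.

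Two things are at stake. The first is precision: baseline VAS is collected but enters only as another outcome level, where a covariate would use it more efficiently. The second is the pilot's purpose. Sizing a full trial needs an effect estimate with its interval for one defined contrast. Here the contrasts depend on a significant interaction, so the plan promises no such estimate, and any estimate that passes the gate has been selected for being large.

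The baseline tests add a smaller problem. At this size, a non-significant result says little about whether the groups are alike.

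**Working it through.** **Is there a figure to reproduce?** No. The protocol states no power, effect size, SD or correlation for VAS.

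**Inputs from the document:** total N = 14, two groups, significance level 5%, four VAS visits.

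**Assumed inputs:** 7 per group (the ratio is not stated), two-sided test for the single contrast, equal SD at all visits, no dropout, effects in SD units, equal correlation r between visits of 0.3, 0.5 or 0.7.

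**Interaction test, no sphericity correction.** Noncentral F with 3 and 36 df:

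λ = (n/2) × Σ(d_t − mean d)² / (1 − r)

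Example: differences 0, 0.5, 1, 0.5 at baseline and weeks 1, 3, 5, with r = 0.5. The mean is 0.5 and the sum of squares is 0.25 + 0 + 0.25 + 0 = 0.5. So λ = 3.5 × 0.5 / 0.5 = 3.5, and power is 0.29.

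**Week-3 ANCOVA.** Noncentral t with 11 df:

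ncp = d₃ × √[(n/2) / (1 − r²)]

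Same example: √(3.5 / 0.75) = 2.16, and power is 0.50. Relative loss = 1 − 0.287/0.504 = 43%.

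**Results by these formulas** (interaction power against week-3 ANCOVA power):

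| Effect at weeks 1/3/5 (SD) | r = 0.3 | r = 0.5 | r = 0.7 |
|---|---|---|---|
| 0.5 / 1 / 0.5 | 0.21 v 0.43 (loss 51%) | 0.29 v 0.50 (loss 43%) | 0.46 v 0.67 (loss 31%) |
| 0.5 / 1 / 1 | 0.28 v 0.43 (loss 35%) | 0.39 v 0.50 (loss 24%) | 0.60 v 0.67 (loss 9%) |
| 1 / 1 / 1 | 0.31 v 0.43 (loss 29%) | 0.42 v 0.50 (loss 17%) | 0.65 v 0.67 (loss 3%) |
| 0.33 / 0.67 / 1 | 0.23 v 0.22 (gain 4%) | 0.32 v 0.26 (gain 22%) | 0.50 v 0.36 (gain 41%) |

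**Simulation as a check.** The ANCOVA formula is slightly optimistic at this size. Simulated ANCOVA power for a 1 SD effect is about 0.40, 0.47 and 0.63 at r = 0.3, 0.5 and 0.7, so the uncorrected losses in the first row become about 47%, 39% and 27%.

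- With a Greenhouse-Geisser correction the losses grow. For 0.5/1/0.5 they are about 49% at r = 0.5 and 58% at r = 0.3, the largest seen.
- For differences of 0.7, 2 and 1 cm with SD 2 cm, corrected interaction power is 0.25 against 0.48 at r = 0.5 (loss 1 − 0.25/0.48 = 48%), and 0.42 against 0.64 at r = 0.7 (loss 34%).
- For a sustained effect at r = 0.7, uncorrected, the two are equal (0.65 against 0.64).
- For the growing profile at r = 0.5, uncorrected, the interaction is ahead (about 0.33 against 0.24 to 0.25).
- With serially decaying correlation of 0.85, the uncorrected interaction also matches or beats week-3 ANCOVA when the effect is sustained or washed out.

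**Baseline tests.** The SE of a baseline mean difference is √(2/7) = 0.535 SD. The chance of an imbalance above 0.5 SD in either direction is P(|Z| > 0.5/0.535 = 0.935) = 35%. The t-test (12 df, ncp = 1/0.535 = 1.87) has about 41% power even for a true 1 SD difference, so it would miss one that large more often than not.

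**The case against.** The strongest reply is that repeated-measures analysis with follow-up contrasts is a standard and valid method, that this is a pilot with no power claim and an acknowledged small sample, and that covariates are commonly settled in a SAP. Most of that stands, and it limits the severity. It does not remove the point, because the article itself fixes the form of the analysis, puts baseline among the outcome levels, and makes the contrasts conditional.

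Four stronger readings are tempting, and the document does not support them.

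- **A general loss of a quarter to a half of the power.** The protocol supplies none of the inputs. Week 3 is the comparator chosen here, since no primary week is named, and that choice favours the criticism when the effect peaks there. The sphericity correction is also an assumption.
- **Baseline imbalance goes wholly unadjusted.** The interaction depends on within-subject differences between visits, so a group offset present at every visit cancels, much as in a change-score analysis. That is less efficient than ANCOVA, but it does use baseline. Having baseline as a level is not in itself an error.
- **Two routes to significance.** Type I error would be 8 to 10% if either a group main effect or an interaction counted as success. The section never says that a main effect counts. For the same reason, the dilution of the main effect by baseline is not decisive.
- **The baseline tests distort the primary analysis.** No exclusion or model choice depends on their result. The wording is wrong, but the consequence is small.

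**Conclusion.** The concern holds in a limited form. A directional hypothesis is routed through a non-directional 3-df interaction that mixes on- and off-treatment visits. No primary week is fixed, baseline VAS is not a covariate, and contrasts are reached only through significance. The analysis is valid. Its weakness is efficiency, and it does not guarantee the one estimate that planning a full trial needs.

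The size depends on assumptions that the protocol cannot settle: 7 per arm, a 1 SD peak effect, the correlation, the time profile and any sphericity correction. The loss against baseline-adjusted week 3 is up to about half when the effect peaks at week 3 and correlation is low to moderate. It is near zero when correlation is high and the effect is sustained, and it turns into a gain if the effect is still growing at week 5. The lack of a guaranteed estimate does not depend on these assumptions.

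This should be fixed. It is not a must-fix, because in the 1 SD scenarios tabulated even the week-3 ANCOVA has power of about two thirds at most with 14 subjects, and the pilot claims no power.

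**What to change.** Reword the Statistical analysis section as follows.

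1. Name one primary time point for VAS. Week 3, the end of treatment, is the natural choice.
2. Compare the arms at that point with baseline VAS as a covariate, either by ANCOVA or by a mixed model for weeks 1, 3 and 5 with the week-3 contrast as primary.
3. Report the adjusted difference with its 95% CI whatever the p-value.
4. Keep the interaction and the week-1 and week-5 comparisons as supportive analyses.
5. Present baseline characteristics descriptively and drop the tests of equivalence.

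The cost is one paragraph. No new data are needed, and the analysis runs in the software already named. Because the Trial status section reports that recruitment has finished, the change should be dated before the allocation is unblinded for analysis. The downside is that the question of how the groups diverge over time becomes secondary, and power is lower than with the interaction if the effect peaks after week 3.

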### Randomization

Subjects will be randomized using a computerized random number generator by an independent statistician who is blinded to subject assignment. The method which we use for randomization concealment is sequentially numbered, opaque sealed envelopes. Block randomization will be performed once a participant’s eligibility is confirmed and written informed consent has been obtained. Treatments will be scheduled after randomization.

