### Safety

The safety of this trial will be determined by red blood cell (RBC) count, hemoglobin level, platelet count, mean corpuscular volume (MCV), mean corpuscular hemoglobin (MCH) level, mean corpuscular hemoglobin concentration (MCHC), hematocrit (Hct), total white blood cell (WBC) count, erythrocyte sedimentation rate (ESR), aspartate aminotransferase (AST), alanine aminotransferase (ALT), blood urea nitrogen (BUN), and creatinine level, serum sodium level, serum potassium level, and serum chloride level. All subjects are evaluated twice, first at the screening visit and once more after the termination of acupuncture treatments. To monitor the safety of the acupuncture treatment, we will monitor the occurrence of edema, hemorrhage, and pain as adverse events.

Any reported adverse events will be recorded throughout the study and vital signs will be monitored at each visit. The subjects will be asked to voluntarily report information about adverse events, and the researcher will confirm the occurrence of adverse events through methods such as a medical interview. Details about adverse events, such as the date of occurrence, degree of severity, causal relationship with the treatment, other treatments or medications that are suspected to cause the adverse event, and treatment of the adverse event will be recorded in detail.

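### Chi-square is fixed as the test for adverse events in a 14-subject trial, where its usual expected-count condition cannot be met and where events attributed to acupuncture have no comparator

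*Protocol article*

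**What the plan says.** The Participants section gives the size of the trial: "A target sample size of 14 subjects with cold hands sensation has been set". The abstract adds the two arms: "A total of 14 subjects will be recruited and randomly allocated to two groups". The control arm receives medication only; the experimental arm receives the same medication plus nine acupuncture sessions.

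For safety, the Statistical analysis section states: "To compare groups and the incidence frequency of adverse events related to acupuncture and medication, the chi-square test will be used". For baseline comparisons it prescribes a "chi-square test for categorical data". The level is 5%. Continuous baseline data have a fallback, the Mann-Whitney test, if normality fails. Categorical data have none.

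The Safety section says of acupuncture that "we will monitor the occurrence of edema, hemorrhage, and pain as adverse events", and provides for the causal relationship of each event with treatment to be recorded.

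**The concern.** There are two problems, and both lie in what the protocol states rather than in what it leaves out.

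1. The chi-square p-value is a large-sample approximation. In a table of 14 subjects the approximation is coarse, and the test can cross the 5% line when the exact probability does not. A pilot meant to inform a larger trial could then report a significant safety difference that an exact test of the same table would not support.

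2. The planned comparison includes events related to acupuncture. Control subjects are not needled, so an event attributed to needling cannot be recorded for them. A test against that zero says nothing useful. A non-significant result might even be taken as reassurance when several needled subjects had such an event.

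**Working it through.** **Inputs.** N = 14 (Participants), two arms (abstract), level 5% (Statistical analysis). The allocation ratio and the expected event rates are not given. The expected-count result below covers every split. The p-values and error rates assume 7:7 and are shown over the possible event totals. The counting unit is the subject.

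The protocol derives no figure on this point, so there is none to reproduce.

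**1. Expected counts.** With arm sizes n1 and n2 and m subjects affected, the smallest expected count is min(n1, n2) × min(m, 14 − m) / 14. Neither minimum can exceed 7, so the bound is 7 × 7 / 14 = 3.5, reached only at 7:7 with exactly 7 affected. In general the bound is N/4, so a minimum of 5 needs N of at least 20. At 7:7, two cells fall below 5 when 1–4 or 10–13 subjects are affected, and all four do when 5–9 are affected.

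**2. Tables where the conclusion changes (7:7).** For a v c affected, Pearson chi-square = 14 × [a(7 − c) − c(7 − a)]² / [7 × 7 × m × (14 − m)], with m = a + c. The 5% critical value is 3.84.

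| Affected | Pearson chi-square | Pearson p | Fisher p |
|---|---|---|---|
| 4 v 0 | 14 × 28² / (49 × 4 × 10) = 5.60 | 0.018 | 2 × 35/1001 = 0.070 |
| 5 v 1 | 14 × 28² / (49 × 6 × 8) = 4.67 | 0.031 | 2 × (147 + 7)/3003 = 0.103 |
| 6 v 2 | 14 × 28² / (49 × 8 × 6) = 4.67 | 0.031 | 0.103 |
| 7 v 3 | 14 × 28² / (49 × 10 × 4) = 5.60 | 0.018 | 0.070 |

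Together with their mirror images, these are the only tables on which the two tests disagree at 5%. Against a count of 0, Pearson is significant from 4/7 and Fisher from 5/7 (p = 0.021).

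**3. Type I error of uncorrected chi-square given the total affected (hypergeometric, 7:7).**

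| Subjects affected | Actual size |
|---|---|
| 1–3 or 11–13 | 0% |
| 4 or 10 | 7.0% |
| 5 or 9 | 2.1% |
| 6 or 8 | 10.3% |
| 7 | 2.9% |

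**4. Unconditional type I error (two binomials with a common rate, 7:7).** For chi-square: 0.03% at an event rate of 5%, 0.3% at 10%, 1.8% at 20%, 3.8% at 30%, 5.2% at 40%, and a maximum of 5.7% at 50%. For Fisher's test the maximum is 1.3%, also at 50%.

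**5. Events attributed to acupuncture.** The control count is fixed at 0. If 3 of 7 needled subjects had such an event, Pearson gives 14 × 21² / (49 × 3 × 11) = 3.82, p = 0.051, and Fisher gives 0.192. Both are non-significant, yet neither answers a real question, because the control rate is known to be zero in advance.

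**The case against.** The expected count of 5 is a rule of thumb. Under a looser minimum of 1, totals of 2 to 12 affected would pass at 7:7. The unconditional error exceeds 5% by 0.7 percentage points at most and is below 5% at event rates up to 30%. The conditional inflation occurs at 4 of 13 possible totals, and at the other nine the size is below 3%. Fisher's test errs the other way, and missing a harm may be the greater worry in a safety comparison. All of this stands. A reader might infer that the planned test is generally anti-conservative; the figures do not show that. If a continuity-corrected chi-square were meant, the four discordant tables would not be significant either (3.15 for 4 v 0 and 7 v 3, 2.625 for 5 v 1 and 6 v 2), but the protocol specifies no correction.

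A reader might also infer that the control arm cannot have any of the events monitored for acupuncture safety. That goes too far. The Discussion lists edema among the side effects of the vasodilators, a class that both arms take, and pain or hemorrhage can also arise without needling. The zero by design covers only events causally attributed to acupuncture.

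A third tempting inference is that nine treatment sessions give the experimental arm more chances to report events, so that the comparison is tilted. The protocol does not establish this. It does not give the number of control visits, events are to be recorded throughout the study, and the statement that "vital signs will be monitored at each visit" draws no distinction between arms. Unequal contact is a possible limitation to mention, no more.

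Finally, no decision rule depends on this p-value. Stopping rests on the principal investigator's judgement of risk, and laboratory tests and vital signs also inform safety. That limits the consequence but does not justify the choice of test.

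**Conclusion.** The point holds in a limited form. For any allocation of 14 subjects, chi-square cannot meet its conventional condition. At 7:7 the uncorrected test gives a different answer from Fisher's exact test on four tables and their mirror images. Its size ranges from 0% to 10.3% given the total affected, with an unconditional maximum of about 5.7%. The same expected-count problem affects the baseline chi-square tests. A between-arm test of events attributed to acupuncture is uninformative; a comparison of medication-related or all-cause events remains meaningful.

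The p-values and error rates assume 7:7 allocation, the subject as the counting unit and no continuity correction. Counting events instead of subjects would not help, because repeated events in one subject are not independent. The practical risk is a misleading p-value in a pilot safety report, and it should be corrected because the correction is cheap.

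**What to change.** - Replace chi-square with Fisher's exact test for adverse events and for baseline categorical data, or report the number of subjects affected per arm with exact confidence intervals and no test.
- Report events attributed to acupuncture descriptively in the experimental arm only, per subject, with an exact interval. For scale, 0 of 7 gives a 95% upper limit of 1 − 0.025^(1/7) = 41%.
- Keep the between-arm comparison for medication-related and all-cause events, including edema, hemorrhage and pain of any cause.
- Mention possible unequal contact between arms as a limitation when the results are interpreted.

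The cost is a change of wording in the Statistical analysis section. It needs no new subjects, visits or data, which matters because recruitment has finished. It should be recorded before safety data are seen by arm.

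The downside is that Fisher's test is conservative (actual size at most about 1.3% at 7 v 7). If the true rates were 50% and 0%, it would reach significance with probability 29/128 = 23%, against 50% for uncorrected chi-square. Exact intervals should therefore accompany or replace it, and a non-significant result should not be read as evidence of safety.
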